### Data analysis

We will use SPSS software version 18.0 (IBM Corp, Armonk, New York, US) to perform data analysis. Demographic and baseline data will be analyzed with standard descriptive statistics. Data will be presented as the mean ± standard deviation (SD). Between-group differences will be tested using repeated-measure analyses of variance (ANOVAs). The entire data analysis process will be performed by statisticians who are independent from the research team and blinded to the group settings. The accepted level of significance for all analyses will be *P* < 0.05.

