**Methods:**

We will recruit a total of 60 participants diagnosed with AS and 30 healthy subjects. Participants will be randomly allocated 1:1 to either an acupuncture group or a sham control acupuncture group. Primary-outcome measures will be musculoskeletal ultrasound, Ankylosing Spondylitis Quality of Life Scale (ASQoL), Bath Ankylosing Spondylitis Metrology Index (BASMI), and the Visual Analogue Scale (VAS) for pain. Secondary outcome measures will be the Bath Ankylosing Spondylitis Disease Activity Index (BASDAI), Bath Ankylosing Spondylitis Function Index (BASFI), and Fatigue Scale-14 (FS-14). We will monitor the effect of acupuncture or sham acupuncture on blood flow and SIJ inflammation using SMI, lumbar-muscle stiffness using SWE and the lumbar paraspinal-muscle cross-sectional area (CSA) using a two-dimensional (2D) grayscale imaging. QoL, physical function, and fatigue will be assessed using an evaluation scale or questionnaire developed for this study, with outcomes measured by the ASQoL, BASMI, BASDAI, BASFI, and FS-14. Healthy subjects will not receive acupuncture but undergo only musculoskeletal ultrasound at baseline. Acupuncture and sham control acupuncture interventions will be conducted for 30 min, 2–3 times/week for 12 weeks. Musculoskeletal ultrasound will be conducted at baseline and post-intervention, while other outcomes will be measured at baseline, 6 weeks, and post-intervention. The statistician, outcome assessor, and participants will be blinded to treatment allocation.

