### Sample size

The required sample size for this study was estimated based on a study by You et al. [47]: at the week 24, pain VAS score was 3.87±1.54 (mean ± standard deviation [SD]) in needle-knife group and 4.59±1.57 in the control group. With a conservative estimate of 0.36point difference on a 10-point VAS score between the two arms, and assuming a standard deviation of 0.72 for both arms, based upon a two sample t tests assuming equal variance analysis conducted by an independent statistician via PASS 15.0, a sample size of 23 per group will yield a power of 90% at an alpha (α) value of 0.05. To account for an anticipated dropout rate of 20%, finally, the sample size was inflated to 60 with 30 patients per arm will be sufficient to detect a clinically important difference in this trial.

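### Repeated-measures ANOVA is named without model term, time point or baseline handling; for ultrasound either available term is less efficient than a baseline-adjusted week-12 comparison

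*Protocol article*

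**What the plan says.** All between-group inference rests on one sentence in the Data analysis section of the protocol article: "Between-group differences will be tested using repeated-measure analyses of variance (ANOVAs". The same section adds: "The accepted level of significance for all analyses will be *P* < 0.05". It does not say whether the group main effect or the group-by-time interaction is the test, which visits enter, or whether baseline is a repeated outcome or a covariate.

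The Methods part of the abstract sets the visits: "Musculoskeletal ultrasound will be conducted at baseline and post-intervention, while other outcomes will be measured at baseline, 6 weeks, and post-intervention". The Primary outcomes section confirms two visits for ultrasound. The Follow-up section adds an assessment 12 weeks after treatment ends, which the legend of Fig. 2 places at week 24.

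The Sample size section works from a different procedure, a comparison at one time: "based upon a two sample t tests assuming equal variance analysis". The source values it cites ("pain VAS score was 3.87±1.54 (mean ± standard deviation [SD]) in needle-knife group and 4.59±1.57 in the control group") are from week 24.

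**The concern.** In a randomised trial the expected arm difference at baseline is zero. If baseline is a level of the time factor, the group main effect averages that zero in with the treatment effect, and the result is a diluted version of the end-of-treatment difference. If the interaction is read instead, two visits give an unadjusted change-score test, and three visits give an omnibus test of any difference in profile, which does not isolate the end of treatment. None of these is the single-time comparison used for sizing.

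Two things are at stake: power in a trial of 30 patients per arm, and clarity about what the reported effect is. With the term left open, it could also be chosen after the data are seen.

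**Working it through.** **1. The plan's own figure.** Inputs from the Sample size section: "With a conservative estimate of 0.36point difference on a 10-point VAS score between the two arms", "assuming a standard deviation of 0.72 for both arms" and "a sample size of 23 per group will yield a power of 90% at an alpha (α) value of 0.05".
- n per arm = 2(1.960 + 1.282)² / (0.36/0.72)² = 2 × 10.51 / 0.25 = 84.1, so 85 (normal approximation) or 86 (exact t test, two-sided).
- The stated 23 is not reproduced. Power at 23 per arm is 38%. A figure of 23 appears only with a difference of 0.72 and an SD of 0.72 (power 91%).
- Dropout: 23/0.8 = 28.75, so 30 per arm is consistent with 23.

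That mismatch is a separate matter. Here it matters only that the sizing is for a t test at one time.

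**2. Ultrasound: baseline and week 12.** Assume equal SD σ at both visits and correlation r, with arm differences 0 and d. Required n is proportional to variance/effect².
- Group main effect: effect (0 + d)/2 = d/2, variance σ²(1 + r)/2, so n ∝ 2(1 + r).
- Group-by-time, which is the t test on change: effect d, variance 2σ²(1 − r), so n ∝ 2(1 − r).
- ANCOVA of week 12 on baseline and arm: effect d, variance σ²(1 − r²), so n ∝ 1 − r².

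The ratios to ANCOVA are 2/(1 − r) for the main effect and 2/(1 + r) for group-by-time.

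| r | main effect / ANCOVA | group-by-time / ANCOVA |
|---|---|---|
| 0.3 | 2.6/0.91 = 2.86 | 1.4/0.91 = 1.54 |
| 0.5 | 3.0/0.75 = 4.00 | 1.0/0.75 = 1.33 |
| 0.7 | 3.4/0.51 = 6.67 | 0.6/0.51 = 1.18 |

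A simulation (effect 0.5 SD, r = 0.5) agrees. The main effect has 46% power at 85 per arm and 90% at 252; the change score has 90% at 85.

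**3. Scales at weeks 0, 6 and 12, if baseline is entered as a level.** Let the week-6 effect be a fraction f of the week-12 effect d, with a common correlation r.
- The main effect estimates (0 + f + 1)d/3, which is d/3, d/2 or 2d/3 for f = 0, 0.5 or 1. Its variance is σ²(1 + 2r)/3, so n ∝ 3(1 + 2r)/(1 + f)². At r = 0.5 the ratios to ANCOVA at week 12 are 6/0.75 = 8.0, 2.67/0.75 = 3.6 and 1.5/0.75 = 2.0.
- The interaction is an F test on 2 and 4(n − 1) degrees of freedom. Its noncentrality is (n/2)·S/(1 − r), where S, the sum of squared deviations of the visit effects from their mean (in SD units), is 2d²/3 for f = 0 or 1 and d²/2 for f = 0.5. For 0.5 SD and 90% power, n per arm is as follows.

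| r | interaction, f = 0 or 1 | interaction, f = 0.5 | ANCOVA | ratio |
|---|---|---|---|---|
| 0.3 | 108 | 143 | 78 | 1.38 to 1.83 |
| 0.5 | 77 | 102 | 65 | 1.18 to 1.57 |
| 0.7 | 47 | 62 | 44 | 1.07 to 1.41 |

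**4. What this means at 30 per arm.** Take the effect in the cited source: SD (1.54 + 1.57)/2 = 1.555, difference 4.59 − 3.87 = 0.72, so 0.72/1.555 = 0.46 SD. With r = 0.5 and two-sided 0.05, power is:
- main effect, two visits: 17.5%; three visits with f = 0.5: 19%
- change score, two visits: 42%
- interaction, three visits with f = 0.5: 33%
- ANCOVA: 53%

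With the anticipated 20% dropout (30 × 0.8 = 24 per arm), ANCOVA power falls to 44%.

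**The case against.** The strongest reply is that the plan does not commit to the unfavourable analysis. A reader might infer that the ANOVA halves the treatment effect and costs four times the patients. The text does not support this as a general statement, for these reasons:
- The model term is not named. With two visits, group-by-time is the change-score test. It estimates the full week-12 effect, is not omnibus, and loses a factor of 1.33 at r = 0.5, not 4.
- Exact halving for the three-visit scales needs baseline as a level, the main effect as the test, and a week-6 effect half that at week 12. Those scales could be analysed on post-baseline visits only, which removes the dilution by baseline.
- Four is neither a ceiling nor typical. It is the value for one case (main effect, two visits, r = 0.5), and the factor reaches 6.7 at r = 0.7.
- Nor can it be said that the reported estimate will not be the end-of-treatment effect, since the text does not say which estimate will be reported.

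It is also fair that under randomisation these tests remain valid tests of no treatment effect, so the issue is efficiency and estimand, not false positives. And a week-12 contrast alone does not match the sizing, whose source values are from week 24.

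A last reply is that model details belong in an analysis plan that is not shown. This answers only part of the point. The article fixes a method, and for ultrasound that method leaves only two between-group terms, both less efficient under equal variances than an analysis using the same data.

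**Conclusion.** The point holds in conditional form. For ultrasound, baseline must be a repeated outcome under the stated method. The cost against ANCOVA is then a factor of 2.9 to 6.7 in patients if the group main effect is tested, which also halves the estimated effect, or about 1.5 to 1.2 if group-by-time is tested (r from 0.3 to 0.7 in both). For the scales, if baseline is a level, the main effect is diluted to between one third and two thirds of the week-12 effect. The interaction costs about 1.1 to 1.8 times the patients and does not isolate the end of treatment.

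These figures assume equal variances across visits and a common correlation. The document gives neither the correlation nor the week-6 profile, so the ranges should be read and not any single value. The existence of a loss for ultrasound does not depend on r: under equal variances both 2/(1 − r) and 2/(1 + r) exceed 1 for any r from 0 up to, but not including, 1.

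**What to change.** Replace the ANOVA sentence in the Data analysis section:
- Ultrasound: ANCOVA of the week-12 value on baseline value and arm.
- Outcomes with several post-baseline visits: a linear mixed model on the post-baseline visits, with baseline value, arm, visit and arm-by-visit.
- In both, report the adjusted arm difference with 95% CI at one pre-stated time point. Week 12 is the natural choice as end of treatment, with week 24 as a further contrast for outcomes measured then.

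Align the Sample size section with the chosen time point, since its source values are from week 24.

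The cost is analysis wording only. Baseline values are already collected, and no visit, measurement or patient is added. The change should be made before unblinding.

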### Ethics and dissemination

All candidates who agree to participate and who meet all of the inclusion criteria and none of the exclusion criteria will be provided informed consent to obtain full understanding of what study participation will entail and the potential risks. Participants have the right to discontinue participation at any time. Data will be used in the aggregate only, and no identifying characteristics of individuals will be published or presented. On the consent form, participants will be asked if they agree to use of their data should they choose to withdraw from the trial. Participants will also be asked for permission for the research team to share relevant data with people from the regulatory authorities, where relevant. This trial does not involve collecting biological specimens for storage.

The study conforms to the principles of the Declaration of Helsinki. Ethical approval has been obtained from the IEC of the Guangdong Provincial Hospital of Chinese Medicine (YF2019-232-01). The trial protocol has been registered at the Chinese Clinical Trial Registry (ChiCTR2000031476). Results will be disseminated through journal articles, a master’s thesis, or conference presentations. Data will be used in the aggregate only, and no identifying characteristics of individuals will be published or presented.

## Discussion

The purpose of this trial is to assess the impact of acupuncture in the management of AS. It is clear that increased muscle stiffness is associated with poor range of motion [48], and a chronic inflammatory condition has significant impact on QoL. Patients report that back pain, arthralgia, and stiffness influence their daily work productivity and nocturnal sleep quality [49]. Acupuncture is used to reduce muscle stiffness and increase somatic activity in AS patients, and it is monitored by musculoskeletal-ultrasound techniques that, if less operator dependent, could obtain more-stable and reliable results [50]. The design of an appropriate control group for a clinical trial is critical. We will set a healthy-control group for baseline comparison, as there is currently no standardized for musculoskeletal-ultrasound measurement of AS. However, it is difficult to use placebo needles for controls. Therefore, we will use non-acupoints and superficial puncturing, which are considered ineffective, in the sham acupuncture group.

NSAIDs are often first-line treatment for AS, and biologics are the next step up. However, patients who have inadequate response to NSAIDs but cannot afford biologics often experience significant pain and impairment of their QoL [51]. This trial would provide evidence for acupuncture care for this group of patients.

Despite the measures taken to ensure a well-controlled trial, there are several methodological limitations to this study. The treatment intervention duration of 12 weeks might make it difficult to ensure patient compliance. Other aspects such as the trial results are meant to describe an approach to treatment for the typical patient and cannot anticipate all possibilities; clinicians must make careful clinical assessments based on sound clinical judgment of each patient’s circumstances and consideration of the patient’s preferences. In spite of its limitations, we hope that the trial will help provide new insights into the value of acupuncture and the evidence of musculoskeletal-ultrasound measures in AS.

### Trial status

This trial is currently recruiting participants. Participants will be recruited for this study started in June 2020 and expected finish in December 2021. The protocol version number is 2019103103, date January 14, 2020.

## Data Availability

Not applicable.

## Abbreviations

AS: Ankylosing spondylitis
QoL: Quality of life
SWE: Wave elastography
SMI: Superb microvascular imaging
SIJ: Sacroiliac joint
BASMI: Bath Ankylosing Spondylitis Metrology Index
ASQoL: Ankylosing Spondylitis Quality of Life Scale
BASDAI: Bath Ankylosing Spondylitis Disease Activity Index
BASFI: Bath Ankylosing Spondylitis Function Index
FS-14: Fatigue scale-14
SAS: Self-Rating Anxiety Scale
SDS: Self-rating depression scale
CSA: Cross-sectional area
NSAIDs: Non-steroidal antiinflammatory drugs
TCM: Traditional Chinese Medicine
ACR: American College of Rheumatology
MRI: Magnetic resonance imaging
OMERACT: Outcome Measures in Rheumatology
OMI: Outcome measurement instrument
SpA: Spondyloarthritis
RCT: Randomized controlled trial
CONSORT: Consolidated Standards of Reporting Trials
STRICTA: Standards for Reporting Interventions in Clinical Trials of Acupuncture
GPHCM: Guangdong Provincial Hospital of Chinese Medicine
SPIRIT: Recommendations for Interventional Trials
HIV: Human immunodeficiency virus
2D: Two-dimensional
RI: Resistance index
PSV: Peak systolic velocity
EDV: End diastolic velocity
VAS: Visual analog scale
SD: Standard deviation
ANOVAs: Analyses of variance
CRF: Case report form
IEC: Institutional Ethics Committee
